### Medication and dosing

The investigator or his/her designee is responsible for explaining the correct use of the investigational agent(s) to the patients and parents, verifying that instructions are followed properly, maintaining accurate records of study drug dispensing and collection, and of returning all unused medication at the end of the study.

This study involves a comparison of an active drug (memantine) with matching placebo. During study period II, medication will be initiated and modified according to the weight group of the patient at BL (visit 3). Dosing may then be increased (or decreased) by 5 mg/day increments, respectively, at specified visits/dates according to the weight of the subject (cf. Table 2). Stepwise up-titration is recommended to the target dose or the highest tolerable dose by week 4, accordingly. Dosing should remain stable during the last 4 weeks of study period II unless a dose reduction is necessary for tolerability or safety reasons. In case of dose-adjustments due to AEs unscheduled visits can be performed (for stepwise down-titration). Patients who cannot tolerate the minimum daily dose specified (5 mg/day) will be discontinued from the study. Investigator decisions on dose changes (up or down) will only be permitted at study visits (or, due to AEs, at unscheduled visits for down-titration). Study medication will be given once daily in the evening, with or without food.

Based on the dosing information from the published literature and considering earlier and ongoing trials with memantine (sponsored by the pharmaceutical company Forest Laboratories, Berlin, Germany) in this age group, dosing was chosen weight-based, accordingly, also taking into account dose-unit availability in Europe (see Table 2).

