### Statistical analysis

#### Clinical efficacy data

The end of the treatment phase will be taken as the primary endpoint. Change from BL in CY-BOCS total score will be used as the primary efficacy variable. As a secondary outcome measure a binary response score will be composed based on the change in CY-BOCS total score and the Clinical Global Impression-Improvement (CGI-I) scale at the end of the treatment phase (at least 30 % reduction in CY-BOCS total from BL and a score of 1 (very much improved) or 2 (much improved) in CGI-I scale). Additional symptom severity scores will be used as secondary efficacy measures.

General linear models will be applied on the CY-BOCS change score to compare the two treatment groups (active drug, placebo). Gender, age, investigational site and BL measurement will be included as covariates. Furthermore, diagnosis and diagnosis by treatment interaction will be entered in the model. A significant interaction effect will be followed up by separate analyses of the two diagnostic groups. In the presence of a high drop-out rate methods for missing data (e.g. last observation carried forwards (LOCF), mixed effect model repeat measurement (MMRM)) will be applied and sensitivity analyses will be performed to assess whether efficacy results are stable across different analysis methods. Logistic regression analyses will be performed to evaluate the effect of treatment on the binary response score. To study the impact of moderating factors on the outcome measures general linear models and logistic regression analyses will be applied, as appropriate. Gender, age, diagnostic group and investigational site will be included as covariates in all analyses. Multivariate statistical analysis of all data will be applied, reducing the chances of identifying false positives. This method can incorporate different types of predictors (clinical patient characteristics as well as neuropsychological and neuroimaging data, genetic and protein data). All analyses will be corrected for multiple testing as appropriate.

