### Withdrawal of individual subjects

Patients can leave the study at any time for any reason if they or their parents wish to do so without any consequences. The investigator can decide to withdraw a subject from the study for urgent medical reasons. Study participation will also be cancelled if patients do not comply with the general directives of the study procedures, or if the investigator decides it is in the best interest of the subject (medical-ethical considerations).

The participating centres have considerable experience with the type of research in paediatric populations proposed in this protocol, and there are limited risks associated with this kind of research.

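### Handling of missing CY-BOCS scores in the primary analysis depends on an undefined high drop-out rate, with LOCF and MMRM unranked, so the week-12 estimate is at risk of bias of unknown size and direction

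*Protocol article*

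**What the plan says.** All references are to the protocol article.

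**Statistical analysis, Clinical efficacy data.** The time point: "The end of the treatment phase will be taken as the primary endpoint". The variable: "Change from BL in CY-BOCS total score will be used as the primary efficacy variable". The model: "General linear models will be applied on the CY-BOCS change score to compare the two treatment groups (active drug, placebo"), with sex, age, site, baseline, diagnosis and diagnosis by treatment as further terms. The condition for missing-data methods, and the methods named: "In the presence of a high drop-out rate methods for missing data (e.g. last observation carried forwards (LOCF), mixed effect model repeat measurement (MMRM"). The same sentence goes on to say that "sensitivity analyses will be performed to assess whether efficacy results are stable across different analysis methods".

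**Medication and dosing.** "Patients who cannot tolerate the minimum daily dose specified (5 mg/day) will be discontinued from the study".

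**Endpoints.** The primary endpoint is the change in CY-BOCS total from baseline to endpoint, for all patients.

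**Table 1.** CY-BOCS is marked at visits 3 to 10 and in the early-discontinuation column. No assessment is described for a patient after that early-discontinuation visit.

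**Sample size calculation.** About 100 patients, 50 per diagnosis, declared insufficient for confirmatory analysis.

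**The concern.** The rule makes the primary method depend on something known only after randomisation, judged against a word with no threshold, assessor or timing. If drop-out is not called high, the text does not say what happens to a patient without a visit 9 score. If it is called high, two methods that estimate different things are offered with no order between them. Both branches leave room to choose a method once results can be seen.

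The missing scores need not be balanced. Intolerance of the minimum dose ends study participation, not only study drug, and intolerance may be more frequent on memantine than on placebo. In the 20–39 kg group, Table 2 lists 5 mg/day at every treatment visit, so there is no lower listed dose to step down to before exit.

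What is at stake is the effect estimate. It is the main product of a pilot trial, and the Discussion offers the data for later marketing-authorisation trial applications.

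**Working it through.** The article gives no SD, effect size, alpha, power or expected drop-out, so there is no figure of the plan's own to reproduce. Every numerical input below is an assumption, chosen to see how the candidate methods behave.

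**Step 1: what the text allows.** A general linear model on a visit 9 change score uses only patients who have that score, so the natural default is completers. The endpoint wording (baseline to endpoint, all patients) and the early-discontinuation CY-BOCS also allow a last-available-value reading, which amounts to LOCF. Both are tested.

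**Step 2: completer bias in closed form.** In one arm, let q be the share who leave and g the number of points by which completers' improvement exceeds that of drop-outs. The full mean is (1 - q) × completers + q × drop-outs, so the completer mean is off by q × g. The error in apparent memantine benefit is therefore q1·g1 - q0·g0 (1 = memantine, 0 = placebo).

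| Drop-out, memantine/placebo | Gap g1/g0 (points) | Error in benefit (points) |
|---|---|---|
| 10%/10% | 4/4 | 0.4 - 0.4 = 0.0 |
| 20%/10% | 4/4 | 0.8 - 0.4 = +0.4 |
| 20%/10% | 4/0 | 0.8 - 0 = +0.8 |
| 30%/10% | 4/0 | 1.2 - 0 = +1.2 |
| 10%/10% | 0/4 | 0 - 0.4 = -0.4 |

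The sign depends on who leaves and why.

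**Step 3: large-sample simulation.** There were 400,000 patients per scenario, assessed at weeks 0, 1, 2, 4, 6, 8 and 12. SD rises from 5 to 8, correlation is 0.85 per visit lag, and placebo changes by -4. Exit is possible after each visit from week 1 to week 8. Three estimators were compared: baseline-adjusted completers, baseline-adjusted LOCF, and a maximum-likelihood equivalent of an unstructured MMRM. In the table, negative values favour memantine.

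| Drop-out mechanism (memantine/placebo) | Completers | LOCF | MMRM |
|---|---|---|---|
| *True effect -4* | | | |
| (i) Completely random, about 22% per arm | -4.01 | -3.43 | -4.02 |
| (ii) Lack of efficacy in both arms, 19%/22% | -3.86 | -3.57 | -4.01 |
| (iii) Intolerance on memantine, unrelated to score, 22%/9% | -4.01 | -3.09 | -4.02 |
| (iv) Memantine exits concentrated in poor responders, 19%/9% | -4.57 | -3.09 | -4.01 |
| (v) Intolerance on memantine, lack of efficacy on placebo, 22%/9% | -3.71 | -3.16 | -4.02 |
| *True effect 0* | | | |
| (iii) 22%/9% | -0.01 | +0.34 | -0.02 |
| (iv) 22%/9% | -0.72 | +0.48 | -0.01 |
| (v) 22%/9% | +0.29 | +0.27 | -0.02 |

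**Step 4: reading the table.** Completers are right in (i) and (iii), too favourable to memantine in (iv), and too unfavourable in (ii) and (v). With a true effect of -4, LOCF pulls towards zero in every row, even under completely random drop-out. In (iv) the two readings of the plan differ by 4.57 - 3.09 = 1.48 points on the same data. Overall drop-out there is (19 + 9)/2 = 14%, which might well not be called high. With no true effect, completers and LOCF in (iv) fall on opposite sides of zero, 0.72 + 0.48 = 1.20 points apart.

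MMRM is close to the truth throughout because every scenario is missing at random or completely at random by construction. The table says nothing about data missing not at random.

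**The case against.** **The article is condensed.** Thresholds, analysis sets and the ranking of methods are often left to the full protocol or SAP. That would answer a complaint about silence. Here the article states a rule, and a plan that follows it inherits the fault.

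**The trial is a pilot.** It claims no confirmatory inference, so no formal decision rests on this estimate. This stands and limits the consequence, but the estimate still matters for later planning.

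**MMRM and a comparison across methods are already named.** True, but both hang on the same undefined condition.

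Three stronger readings are tempting and are not supported:

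- *That the primary analysis is a completer analysis.* The article names no analysis set, and the endpoint wording and early-discontinuation CY-BOCS allow a last-available-value reading.
- *That patients leaving early are lost to assessment altogether.* Table 1 marks CY-BOCS, CGI-S and CGI-I at early discontinuation; only later assessments are absent.
- *That poor adherence to study drug removes patients.* Withdrawal of individual subjects says "Study participation will also be cancelled if patients do not comply with the general directives of the study procedures", which concerns study procedures. Treatment compliance describes counselling for missed medication and states no removal.

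**Conclusion.** The point holds as a risk. The missing-data rule is badly fixed: its trigger is undefined and can be judged after the data are seen, its two named methods are unranked, and the sensitivity analyses share the same condition. Exit for intolerance makes it plausible, not certain, that missing week-12 scores differ by arm.

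A reader might infer that the memantine effect will be biased, or biased in a known direction. The documents do not support that. They give no drop-out rates or reasons, and in the scenarios above completer bias is nil, positive or negative according to the assumed mechanism. For a true effect of -4 the illustrative ranges are -3.71 to -4.57 for completers and -3.09 to -3.57 for LOCF, with MMRM at about -4.0 under missing at random. These ranges rest on the assumed SD, correlation, course and drop-out mechanisms, and are not forecasts for this trial.

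**What to change.** 1. Make a likelihood-based MMRM the primary analysis whatever the drop-out rate. Include all randomised patients with a baseline and at least one post-baseline CY-BOCS from visits 4 to 9, with the treatment contrast at visit 9. Adjust for baseline, site, sex, age, diagnosis and diagnosis by treatment.
2. With about 100 patients and six post-baseline visits, prespecify the covariance structure and a fallback if the model does not converge. State how an early-discontinuation score is assigned to a visit, and that visit 7 scores are collected by telephone.
3. Remove LOCF as a main option.
4. Prespecify a delta-adjusted or reference-based sensitivity analysis, to be run unconditionally, because MMRM alone relies on data being missing at random.
5. Optionally, state that stopping study drug does not by itself end outcome collection, so that a visit 9 CY-BOCS is sought where consent continues. This changes no dose or clinical stopping rule.

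Items 1 to 4 change the analysis text and add a little analysis work; MMRM is already named and the visits are already in Table 1. Item 5 is a procedural change at the sites and adds a few assessments in patients who stopped early. All should be settled before unblinding.

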#### Tolerability/Safety data

To analyse tolerability and safety of the medication logistic regression analysis will be performed on the indicator variables for AEs, and Poisson regression will be used for the number of AEs. Gender, age, diagnostic group and investigational site will be included as covariates in all analyses.

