### Study population

Overall, *N* = 100 patients (*N* = 50 participants with OCD and *N* = 50 participants with ASD), male or female, with inpatient or outpatient status, aged 6 years (ASD patients)/8 years (OCD patients) to 17 years and 9 months at inclusion, will be randomised into study period II. These patients will be recruited from four centres, i.e. per site approx. *N* ≥24 children and adolescents (*N* = 12–13 with OCD; 12–13 with ASD).

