### Randomisation

Randomisation will be done in a 1:1 ratio (active drug: placebo).

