### Sample size calculation

The total sample size of approx. *N* = 100 paediatric patients (*N* = 50 in each diagnostic subgroup (OCD, ASD)) across trials will not allow for confirmatory statistical analyses but will be adequate for descriptive statistics, for pilot-testing of the chosen glutamatergic medication (memantine), and for hypothesis generation.

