### Endpoints

The endpoint for primary objective 1 (clinical effectiveness) is the baseline-to-endpoint change of compulsivity as measured by the CY-BOCS total score (all patients). The endpoints for primary objective 2 (tolerability and safety) are adverse event (AE) rates, derived from both spontaneous reporting and a structured AE instrument, the (adapted) Pediatric Adverse Event Rating Scale (PAERS; [57]).

The endpoints for the secondary objectives (other effects) are additional clinical outcomes, e.g. response rates, response defined as at least 30 % reduction versus BL on the primary outcome scale (CY-BOCS total score, for OCD, ASD patients) plus Clinical Global Impressions-Improvement (CGI-I; [53, 54]) score of 1 (very much improved) or 2 (much improved); baseline-to-endpoint changes in the total score of the Aberrant Behaviour Checklist-Community (ABC-C; [58–60]: ASD patients).

For the tertiary objective (genetic pathways) genotypes of single common and rare variants in candidate genes, and also combined genetic variants in whole genes or neurotransmitter systems/gene pathways will be investigated and further laboratory assessments of various proteins in blood plasma will be performed. Neuroimaging data will be analysed according to the TACTICS COMPULS protocol (see below) in order to explore the effects of glutamatergic interventions at the level of the structure, function and biochemistry of the fronto-striatal circuits.

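### The adverse-event analysis names Poisson regression for counts and one full covariate set for every event indicator, so intervals are too narrow if counts are overdispersed and models for infrequent events are fragile

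*Protocol article*

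**What the plan says.** Under Endpoints: "The endpoints for primary objective 2 (tolerability and safety) are adverse event (AE) rates", taken from spontaneous reports and from a structured rating scale.

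Under Tolerability/Safety data two model types are named: "logistic regression analysis will be performed on the indicator variables for AEs, and Poisson regression will be used for the number of AEs". The next sentence sets the adjustment: "Gender, age, diagnostic group and investigational site will be included as covariates in all analyses".

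The Study population section adds "These patients will be recruited from four centres". The Sample size calculation section gives "The total sample size of approx. *N* = 100 paediatric patients" and says that this number "will not allow for confirmatory statistical analyses but will be adequate for descriptive statistics". Allocation is 1:1, so about 50 patients per arm.

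Three other places bear on the point:

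- The Safety evaluations section has events elicited at each visit, first by open questioning and then by the rating scale.
- The Medication and dosing section provides that patients who cannot tolerate the lowest daily dose leave the study.
- The section on study period III lets only completers of the 12-week period enter the down-titration week, and Table 1 still lists AE monitoring at the visit that ends that week.

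**The concern.** Three features of the stated analysis fit poorly with the data it will meet.

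1. **Counts.** Poisson regression takes the variance to equal the mean. Events are asked about repeatedly in the same child, and some children and parents will report many more than others. Extra between-patient variation is therefore plausible, and it makes the model-based standard errors too small.
2. **Number versus rate.** The endpoint is a rate, but the modelled quantity is the number of events. If one arm stops earlier on average, it has less time to report and its count falls for that reason alone.
3. **Covariates.** The same set, including site, is required for every AE indicator, however few patients have the event. Small numbers spread over four sites leave some sites with no events.

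The trial offers estimates and intervals rather than a confirmatory test, and its Discussion section expects the data to inform later trial applications. Intervals that are too short, or model output that cannot be interpreted, would weaken one of its two primary objectives.

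**Working it through.** The protocol article states no event rate, dispersion, dropout or alpha, so there is no figure of its own to reproduce. A two-sided 5% level and the ranges below are assumptions.

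**Parameters.** Gender 1, age 1, diagnosis 1, site 4 − 1 = 3, giving 6 covariate parameters. Adding treatment gives 7 slopes. At 10% incidence there are 100 × 0.10 = 10 patients with the event, or 10/7 = 1.4 per slope. At 5% there are 5/7 = 0.7.

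**Overdispersed counts.** With variance/mean ratio φ, the Poisson interval has 1/√φ of its correct width. A nominal 5% test then rejects with probability 2[1 − Φ(1.96/√φ)]. Null trials were simulated with 100 patients, the stated covariates, gamma-Poisson counts, a mean of 1 to 3 events per patient, and 1,000 to 1,500 runs per setting.

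| φ | Width ratio 1/√φ | Too narrow by | Type I error, formula | Type I error, simulated |
|---|---|---|---|---|
| 1 | 1.00 | 0% | 5% | 4-6% |
| 1.5 | 0.82 | 18% | 11% | 10-11% |
| 2 | 0.71 | 29% | 17% | 16-17% |
| 3 | 0.58 | 42% | 26% | 23-27% |

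With a Pearson-scaled standard error the simulated type I error was 4-7% in every setting.

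**Unequal time at risk.** Suppose those who drop out do so halfway on average and the true rate ratio is 1. The apparent ratio from unadjusted counts is (1 − 0.5·d₁)/(1 − 0.5·d₀), where d₁ and d₀ are the dropout proportions on memantine and placebo.

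- 20% v 20%: 0.90/0.90 = 1.00
- 20% v 10%: 0.90/0.95 = 0.95
- 30% v 10%: 0.85/0.95 = 0.895

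With Poisson counts of mean 2, simulated type I error at 30% v 10% was 11.6% without an offset and 4.3% with log exposure as offset. At 20% v 20% it was 6.4% and 4.9%.

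**Infrequent events.** Three sets of simulations of the full-covariate logistic model (400 to 1,000 data sets per incidence) gave the figures below. The last column is the chance that at least one arm of 50 has no event, 2(1 − p)^50 − (1 − p)^100.

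| Incidence p | Fits with any non-finite coefficient | Treatment odds ratio inestimable |
|---|---|---|
| 5% | 73-78% | 2(0.0769) − 0.0059 = 14.8% |
| 10% | 27-32% | 2(0.00515) − 0.00003 = 1.0% |
| 15% | 7-9% | about 0% |
| 20% | 1-3% | about 0% |

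Simulation of the treatment term agreed: 13-15% at 5% incidence and about 0.5% at 10%. The gap between the two columns is due to the required covariates, chiefly sites without events. At 30% incidence and above no fit failed.

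**The case against.** The strongest reply is that this is a journal article and the analysis plan is not shown. An exposure offset, a dispersion adjustment, a rule for sparse events and a definition of on-treatment events are ordinary contents of such a plan, and nothing in the text forbids them. An endpoint called a rate is itself compatible with an offset. This reply stands in part: the absence of these details is not an error. It does not dispose of the point. The text names the count model, and it requires the full covariate set in all analyses, so a later plan that dropped site for rare events would depart from it.

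The second reply is that most non-finite coefficients are nuisance terms. This is correct. A site without events gives a divergent site term while the treatment estimate usually stays finite. A reader might infer that safety models generally fail, or that most rarer events yield infinite treatment odds ratios. The figures above do not support either.

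The third reply is that the trial disclaims confirmatory testing and states no alpha for safety, so type I error is a weak yardstick. That is fair, but interval width matters as much in a descriptive trial.

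Three further inferences go beyond the text:

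- **That harm will be hidden.** The direction and size of any bias depend on dropout by arm, which the protocol article does not predict.
- **That events before the first dose enter the counts.** Table 1 schedules AE monitoring from visit 2, but a collection schedule is not a counting rule. Such events would also be balanced in expectation by randomisation.
- **That the responder analysis needs the same change.** For it the article says only "Logistic regression analyses will be performed to evaluate the effect of treatment on the binary response score" with the common covariates. No response rate is given, so nothing shows that this model is overloaded.

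**Conclusion.** The point holds in conditional form. For a primary-objective endpoint, the stated methods are less robust than readily available alternatives.

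- **Counts:** intervals are 18-42% too narrow at an assumed variance/mean ratio of 1.5 to 3, and correct if there is no overdispersion.
- **Rate ratio:** an apparent value of about 0.90 under a true value of 1 at an assumed 30% v 10% dropout, and no bias on average if dropout is equal.
- **Indicators:** below about 10% incidence the required covariates often make the fitted model degenerate, while the treatment odds ratio is lost in about 15% of trials at 5% and 1% at 10%. At 20% or more the models nearly always fit.

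Confidence is medium, because incidence, dispersion and dropout are all assumed. The change is worth making before the data are analysed, but the consequence is for the reliability of exploratory safety estimates and not for a confirmatory claim.

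**What to change.** Amend the Tolerability/Safety data paragraph, or settle the same points in the analysis plan and state there that it supersedes the paragraph.

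1. **AE counts:** negative binomial regression, or Poisson regression with a scaled standard error, with log time at risk as offset. Count events that start or worsen after the first dose.
2. **Infrequent AE indicators:** risk differences between arms with score or exact 95% confidence intervals in place of the mandatory full-covariate logistic model. If a model is wanted, use Firth-penalised logistic regression with treatment and diagnosis only. Fix the threshold in advance. About 20 patients with the event would be consistent with the calculations above.
3. **Common AE indicators:** the stated logistic model can stay.

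The responder analysis needs no change on this ground.

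The cost is about two sentences of wording. No new data are needed, because time at risk follows from dates a trial records anyway. The downside is slightly wider intervals and, for infrequent events, no adjustment for site, gender or age.

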### Aims and objectives

#### Primary objectives

To investigate: clinical effectiveness of the glutamatergic compound memantine in paediatric patients with OCD (GOAT-1) and ASD (GOAT-2) with respect to symptoms of ‘compulsivity’ (assessed as total score of the Children’s Yale-Brown Obsessive-Compulsive Scale (CY-BOCS; [52])) and to explore tolerability and safety (based on, e.g. laboratory measures, electrocardiography (ECG), adverse events) of the compound memantine in these clinical indications.

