Patients treated with glutamatergic compounds and their parents will have the benefit of potential medication effects on their symptomatology and the related burden of illness (reductions), plus of respective improvements in health-related quality of life. Equally important, all patients and parents can benefit from the high frequency and intensity of care – offered via the study visits by experienced child and adolescent psychiatry staff – that in general clearly extends beyond routine care settings.

An acute treatment period of as long as 12 weeks was chosen in order to increase the chance to reflect change/improvement based on medication treatment. With applying the respective adequate instruments, clinical outcome parameters will reflect compulsivity symptom clusters, but also comprehensive information on psychosocial functioning and health-related quality of life relevant in child and adolescent development. Contrasting findings across the patient populations will allow the assessment of disorder-related variation.

It is believed that the proposed project – with performing this pilot clinical trial in populations of children and adolescents with compulsivity disorders – will help to elucidate efficacy/effectiveness and tolerability/safety of glutamatergic medications, further to explore effects of moderating and mediating factors on the response to these compounds. Also, findings will allow assessment of medication effects on biomarkers and neural mechanisms underlying compulsivity. In addition, these pilot data will be made available to be used for potential future Paediatric Use Marketing Authorisation (PUMA) directed trial applications.

Respective MRI/MRS findings (from subgroups of patients, combined with the data from the TACTICS project’s COMPULS study) will help to clarify which mechanisms count for the compulsive behaviours in the considered disorders and subsequently to understand the links between compulsivity, impulsivity and addiction. These understandings will provide a basis for prospectively developing a guide for clinicians as to whether children are at high risk for negative outcome as severe compulsive behaviours and addictive behaviours in adolescence and adulthood.

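### The adverse-event models name diagnosis only as a covariate, so as written they give one memantine effect averaged over OCD and ASD, although safety is a primary objective in both disorders

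*Protocol article*

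**What the plan says.** Under Primary objectives, the protocol article sets out to examine effectiveness in OCD (GOAT-1) and ASD (GOAT-2), and "to explore tolerability and safety (based on, e.g. laboratory measures, electrocardiography (ECG), adverse events) of the compound memantine in these clinical indications". Under Endpoints it adds: "The endpoints for primary objective 2 (tolerability and safety) are adverse event (AE) rates".

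The section Tolerability/Safety data gives the analysis: "logistic regression analysis will be performed on the indicator variables for AEs, and Poisson regression will be used for the number of AEs". On the other model terms it says: "Gender, age, diagnostic group and investigational site will be included as covariates in all analyses". It mentions neither a treatment-by-diagnosis term nor an analysis by diagnosis.

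The section Clinical efficacy data treats CY-BOCS change differently. After listing the covariates it says: "Furthermore, diagnosis and diagnosis by treatment interaction will be entered in the model". It continues: "A significant interaction effect will be followed up by separate analyses of the two diagnostic groups".

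The Discussion says: "Contrasting findings across the patient populations will allow the assessment of disorder-related variation".

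**The concern.** A covariate for diagnosis lets the background AE rate differ between OCD and ASD. It does not let the memantine effect differ, because on the logit or log scale the model has one treatment coefficient for both disorders. The protocol article itself separates the two ideas for CY-BOCS, where diagnosis and its interaction with treatment are both named. For AEs only the covariate is named, and no reason is given.

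If memantine were tolerated differently in the two disorders, the modelled result would be an average that describes neither. It would understate the excess of AEs in one disorder and overstate it in the other. The Discussion expects the data to be available for possible later paediatric marketing-authorisation applications. A follow-on trial in one indication would want the AE contrast for that indication.

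**Working it through.** **Inputs from the protocol article.** There are 50 OCD and 50 ASD patients (Sample size calculation), randomised 1:1 (Randomisation). That gives about 50/2 = 25 per arm within each disorder and 50 per arm pooled. The article gives no AE rates, power or effect size, so it has no figure to reproduce.

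**Assumptions.** All AE rates below are assumed for illustration, with exactly 25 patients per cell. Gender, age and site are left out of the calculation.

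**1. Logistic model, harm in one disorder only.** Assume placebo 20% in both disorders, memantine 20% in OCD and 44% in ASD. The counts with an AE are 5/25 vs 5/25 in OCD, and 11/25 (memantine) vs 5/25 (placebo) in ASD.

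- OCD odds ratio: (5 × 20)/(20 × 5) = 1.00.
- ASD odds ratio: (11 × 20)/(14 × 5) = 220/70 = 3.14.
- Main-effects logistic fit (treatment + diagnosis): common odds ratio 1.91, 95% CI 0.76 to 4.79.
- Hand check by Mantel-Haenszel: (220/50 + 100/50)/(70/50 + 100/50) = 6.4/3.4 = 1.88.

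**2. Other assumed rates, again with no effect in the second disorder.**

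| Placebo vs memantine, affected disorder | Odds ratios by disorder | Common odds ratio |
|---|---|---|
| 10% vs 40% | 6.00 and 1.00 | 3.14 |
| 20% vs 50% | 4.00 and 1.00 | 2.20 |
| 30% vs 60% | 3.50 and 1.00 | 1.94 |

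In the extreme case of opposite effects (20% to 40% in one disorder, 40% to 20% in the other), the common odds ratio is 1.00.

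**3. Poisson model.** With equal cells, the common rate ratio is the summed memantine rates over the summed placebo rates. True rate ratios of 2 and 1 give (2 + 1)/(1 + 1) = 1.5. Ratios of 3 and 1 give (3 + 1)/(1 + 1) = 2.0.

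**4. Precision of estimates by disorder.** The 95% half-width of a risk difference is 1.96 × √(2p(1 − p)/n).

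| AE rate p | n = 25 per arm (one disorder) | n = 50 per arm (pooled) |
|---|---|---|
| 20% | ±22 points | ±16 points |
| 40% | ±27 points | ±19 points |

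The ratio is √(50/25) = 1.41.

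**5. What the by-disorder estimates could show in the example of step 1.**

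- ASD: the SE of the log odds ratio is √(1/11 + 1/14 + 1/5 + 1/20) = 0.642, so the 95% CI is about 0.89 to 11.1. The risk difference is 24 points (about −1 to +49).
- OCD: the SE is √(1/5 + 1/20 + 1/5 + 1/20) = 0.707, so the 95% CI is 0.25 to 4.0.
- Ratio of the two odds ratios: 3.14, with SE √(0.642² + 0.707²) = 0.955 and 95% CI about 0.48 to 20.

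**6. Power (two-sided 5% assumed).** The range covers placebo rates of 10 to 30% and an excess of 20 to 40 points in one disorder only. The interaction test has about 17 to 49% power, the pooled comparison about 18 to 71%, and the comparison within the affected disorder about 30 to 90%.

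**The case against.** A fair defence has four parts.

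**The covariate sentence does not exclude an interaction.** The same sentence stands in the efficacy section beside an explicit interaction term, and the safety section does not list its model terms in full. This stands as a caution: the point concerns the models as written, not a declared refusal to look by disorder. The efficacy section does, however, name the interaction separately when it is intended.

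**AE tables by diagnosis belong in the analysis plan.** Nothing excludes them, the sample is described as adequate for descriptive statistics, and the Discussion promises contrasts between populations. This also stands, so the absence of such tables from the article is not the point. What remains is that the models it does specify do not match the two-indication objective.

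**The trial is exploratory and small.** Pooling for precision is defensible, and the pooled interval in the example (0.76 to 4.79) contains both disorder-specific values, 1.0 and 3.14. The interaction test is weak. This rules out a powered test, but not estimates with intervals. The protocol article accepts the same limitation when it fits the interaction for CY-BOCS.

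**The difference between disorders is hypothetical.** That is correct: the document gives no reason to expect memantine AEs to differ by disorder.

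A reader might go further and infer that the plan cannot reveal a harm confined to one disorder, or cannot answer its safety objective. The documents do not support either reading. Such a harm would still appear, diluted, in the pooled estimate (except where effects in the two disorders cancel). AEs are collected at each visit by open questioning and a structured scale, and tables by diagnosis remain possible. The objective is to explore, and the endpoint is AE rates with no stated requirement by disorder.

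**Conclusion.** The point holds as a mismatch between the stated AE models and a primary objective that covers two disorders. As written, the models give one memantine effect averaged over OCD and ASD, while the CY-BOCS model allows two. Under the assumed rates in which only one disorder is affected, the common odds ratio falls well between the two disorder-specific values: 1.9 against 1.0 and 3.1, or 2.2 against 1.0 and 4.0. These sizes rest on assumed AE rates and on 25 patients per cell. With no difference between disorders there would be no dilution of this kind.

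The conclusion does not extend to saying that a harm would be missed, or that a by-disorder analysis would establish one. At this sample size it would yield descriptive estimates with wide intervals.

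**What to change.** In Tolerability/Safety data, state that for overall AE occurrence and for number of AEs the treatment contrast (risk difference or rate ratio, with 95% CI) will be estimated within OCD and within ASD. A diagnosis-by-treatment term, as for CY-BOCS, is one way to do this. Report these estimates descriptively whatever the interaction p-value, beside the pooled diagnosis-adjusted estimate. Keep sparse single AE terms in descriptive tables by arm and diagnosis.

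The cost is a sentence or two of analysis text and one more table from data already collected. The intervals by disorder will be about 1.4 times as wide as the pooled ones. They should be labelled descriptive and not read as confirming or excluding a difference between disorders.
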